## Methods/Design

### Study design

*HeadCoach* will be evaluated via a cluster randomised controlled trial (RCT) conducted within three industry partner organisations. Clusters will comprise of groups of managers based on organisational-specific pre-existing geographical work zones to reduce the risk of contamination between the intervention and control groups. Stratification will occur based on the number of managers within each zone for each industry. A researcher independent from the trial will use a computer-generated program to conduct the stratified randomisation of workplace zones prior to recruitment. Outcome data will be collected from the managers and from employees who report directly to them.

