### Statistical analysis

Primary analyses will be undertaken within an intent-to-treat framework, retaining all participants as randomised, regardless of extent of engagement with training or withdrawal from the study. Likelihood based methods (mixed-model repeated measures (MMRM)) will be used to assess significance of change in the two primary manager outcome measures. Clustering will be accommodated by a random cluster membership (work site) factor. A priori planned comparisons of change from baseline to the 4-month endpoint will test the primary hypothesis. An unstructured variance-covariance matrix will be used to accommodate relationships between observations at different occasions of measurement. Stratification variables and any variables found to be substantially imbalanced between intervention arms post randomisation will be tentatively included in these models and retained if statistically significant and influential on outcomes. Length of time from baseline to complete training and associated post-intervention assessment will also be introduced tentatively into models to evaluate the effects of adjustment for possible effects associated with some managers undertaking these assessments earlier than others and earlier than control group participants.

Similar analyses of scaled secondary manager outcomes will assess differential change due to intervention arm. Mathematical transformation or categorisation of raw scores may be undertaken to meet distributional assumptions and address any violation of assumptions attributable to outliers. Comparable analyses of employee measures will additionally accommodate the nesting of employees within managers by including a random effect for managers where this is possible.

Additional per-protocol analyses to assess effectiveness of the program will focus on managers who completed at least one of the three topics. This subgroup will be compared to all responders in the waitlist control group and, secondarily, with managers who completed less of the training material. The latter comparison will inform the dose-response profile of the intervention and, in particular, whether completing only a subset of the earlier components of *HeadCoach* has a benefit comparable to the complete program.

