All tests of treatment effects will be conducted using a two-sided alpha level of 0.05 and 95% confidence intervals. A member of the research team who is blinded to the intervention and waitlist control allocations will perform this analysis. The nature of the intervention will make blinding managers to their group allocation impossible.

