### Sample size and power calculations

Our industry partners comprise a total of 42 geographical clusters with an average of 20 managers in each cluster. Participation in this study will be voluntary. Based on pilot data, we assume a conservative participation rate of 20% of all managers, with a drop-out rate of 25%. Based on these assumptions, we anticipate being able to recruit a minimum of 168 managers and to successfully follow up 126. Assuming an intraclass correlation of 0.05 yields a design effect of 1.15, the forecast achievable sample size would have 80% power to detect a moderate effect size of 0.54 using an alpha value of 0.05.

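### The primary model keeps stratification factors and imbalanced covariates only if they prove significant and influential, so it is selected from outcome data and may not match the stratified randomisation

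*Protocol article*

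**What the plan says.** The Study design section describes how zones are allocated: "Stratification will occur based on the number of managers within each zone for each industry". The Statistical analysis section specifies a mixed model for repeated measures with a random cluster factor and an unstructured covariance matrix. It names the primary test: "A priori planned comparisons of change from baseline to the 4-month endpoint will test the primary hypothesis".

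The same section then sets a rule for the covariates of these models. It covers "Stratification variables and any variables found to be substantially imbalanced between intervention arms post randomisation", and such variables "will be tentatively included in these models and retained if statistically significant and influential on outcomes". Time from baseline to finishing training and to the associated assessment "will also be introduced tentatively into models to evaluate the effects of adjustment".

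Two further statements bear on the point: "All tests of treatment effects will be conducted using a two-sided alpha level of 0.05", and "A member of the research team who is blinded to the intervention and waitlist control allocations will perform this analysis".

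**The concern.** The rule makes the content of the primary model depend on the outcome data. This has two consequences.

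First, the stratification factors are expressly subject to the rule and can be removed. Stratified allocation balances stratum effects between arms. If those effects matter for the analysed quantity and are left out, they stay in the error term, the standard error is too large, and the test is conservative.

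Second, other covariates enter because they happen to be imbalanced and stay because they are significant. A test computed after such a step does not have a guaranteed error rate, and different reasonable applications of the rule give different primary estimates, intervals and p-values. The imbalance need not be pure chance either. Zones are randomised before recruitment and managers opt in afterwards, so it may reflect who chose to take part. That is a reason to name prognostic covariates in advance. Screening by p-value does not deal with it.

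**Working it through.** **The plan's own figure.** From Sample size and power calculations ("Our industry partners comprise a total of 42 geographical clusters with an average of 20 managers in each cluster", 20% participation, 25% drop-out, intraclass correlation 0.05, effect size 0.54):

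- Recruited: 42 × 20 × 0.20 = 168. Followed up: 168 × 0.75 = 126.
- Design effect with 4 recruited managers per zone: 1 + (4 − 1) × 0.05 = 1.15.
- Effective number: 126 / 1.15 = 109.6, or 54.8 per arm (1:1 allocation assumed).
- Power at 0.54, two-sided 0.05: 0.807 by the normal formula, 0.800 by the t distribution. The stated 80% is reproduced.

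This formula has no covariate term, so the point leaves the stated sample size and power untouched.

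**How dropping strata could hurt.** Assume strata explain 10% of outcome variance, the residual zone correlation is 0.03, and 126 / 42 = 3 managers are analysed per zone.

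- Zone-mean variance with strata in the model: 0.9 × (0.03 + 0.97/3) = 0.318.
- With strata left in the error term: 0.318 + 0.100 = 0.418.
- The standard error is too large by a factor of √(0.418/0.318) = 1.147.
- The test then behaves as if the critical value were 1.96 × 1.147 = 2.25, a two-sided type I error of about 2.5%.

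This is for a single follow-up outcome with no baseline, and with the strata always dropped.

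**The rule itself, significance only.** Zone-level simulation of a single follow-up outcome, 6,000 runs per setting, Monte Carlo standard error of type I error about 0.003. The 42 zones and correlation 0.05 come from the protocol, and 3 managers per zone follows from it. The rest is assumed: six strata, five candidate covariates with coefficient 0.2, imbalance cut-off 0.2 SD, retention at p < 0.05. The fixed model holds strata and all five covariates; the last column in each group uses neither.

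| Between-stratum SD | Strata dropped by rule | Type I: rule | Type I: fixed model | Type I: strata ignored | Power at 0.54: rule | Power: fixed model | Power: strata ignored |
|---|---|---|---|---|---|---|---|
| 0 | 95% | 0.051 | 0.045 | 0.048 | 0.744 | 0.727 | 0.738 |
| 0.1 | 91% | 0.057 | 0.049 | 0.052 | 0.740 | 0.730 | 0.733 |
| 0.2 | 75% | 0.052 | 0.049 | 0.038 | 0.722 | 0.729 | 0.695 |
| 0.3 | 46% | 0.051 | 0.053 | 0.030 | 0.724 | 0.726 | 0.661 |
| 0.4 | 18% | 0.052 | 0.047 | 0.023 | 0.736 | 0.747 | 0.616 |

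With strata only and no covariates, power at SD 0.4 is 0.742, so ignoring strata there costs 0.742 − 0.616 = 0.126. The absolute powers are not comparable with the stated 80%, because the covariates add outcome variance and the test uses zone-level degrees of freedom.

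Two things follow. With 42 zones, a significance test often discards strata of moderate influence (75% of trials at SD 0.2). Yet the rule's type I error stays at 0.051 to 0.057, and its power is between 1.1 points below and 1.7 points above the fixed model.

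**The planned contrast.** The primary test is on change from baseline. A stratum effect that shifts baseline and 4-month scores equally cancels in the difference; only a stratum effect on change remains. A zone-level simulation of change scores under the significance rule gave type I error of 5.2 to 5.8%, against 4.8 to 5.8% with strata always kept, and power within about 1 point.

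**The case against.** The strongest reply is that no material damage to the primary contrast has been shown, and much of this stands. In a simulation of the change contrast with known covariance (42 zones of 4 managers, 25% drop-out, six strata explaining 10% of variance, assumed within-person correlation 0.6, 1,500 runs per cell), dropping against keeping the strata gave standard errors of 0.1457 and 0.1455, type I error of 3.9% in both, and power of 95.6% and 95.5%. The rule also tends to keep the strata that matter most.

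A reader might infer that the test is seriously conservative. One zone-mean simulation gives 2.4% type I error and 77% power without the strata, against 4.8% and 85% with them. Those figures describe strata that are always dropped from a model without baseline, which is neither the stated rule nor the planned contrast.

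A reader might equally infer marked inflation. Type I error reaches 8.2% in a simulation with eight assumed covariates, but only if a covariate is kept when it moves the estimate away from zero. The protocol speaks of influence on outcomes and gives no direction. With imbalance and significance alone, the same simulation gives 4.1%.

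Two defences do not remove the point. The blinded analyst guards against deliberate steering, but the model still depends on the data. And although this is a condensed article whose thresholds may be defined in an analysis plan, the objection is to a rule the article states. A plan that followed it faithfully, with every threshold defined, would still select the primary model from outcomes.

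**Conclusion.** The point holds in a limited form. The protocol fixes the contrast, the cluster term, the covariance structure and the alpha level, but it lets outcome data decide whether the randomisation strata and imbalanced covariates are in the primary model. The main harm is that the primary estimate, interval and p-value hang on that selection, and that the analysis may not match the stratified allocation.

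The numerical effect is expected to be small: type I error of about 5 to 6% and a power change of about 1 point under significance-only selection. It would be larger, as a conservative test, only if strata that predict change were dropped. These sizes rest on assumed strata, covariate strengths and thresholds. How influence would be judged is not stated and was not modelled in the table. The documents do not support a claim that the primary test is invalid. This is a cheap improvement that should be made, not a flaw that must be repaired before the trial can be relied on.

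**What to change.** Replace the retention rule with a fixed specification of the primary model:

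- Include the stratification factors (organisation and zone size) whatever their p-values. If baseline is a response in the mixed model, include their interaction with time as well, because a stratum main effect alone does little for a change contrast.
- Use baseline confidence once, either as a response or as a covariate, not both.
- Name any other prognostic covariates before unblinding, and delete retention by significance.
- Move adjustment for observed imbalance to a named sensitivity analysis.

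The cost is a reworded sentence or two and about 5 degrees of freedom per set of stratum terms, taking three organisations by two size bands as an assumption (6 − 1 = 5). If the strata turn out not to be prognostic, about 1 to 2 points of power are lost: 0.744 − 0.727 = 0.017 in the first row of the table, where the fixed model also carries five covariates, and 83% against 81% in a separate zone-mean simulation. The target of 168 managers and the stated 80% power are unchanged.

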#### Managers

At the completion of the baseline data collection period for employees, managers will be invited by email to participate in the study irrespective of whether their employees responded to the baseline questionnaire. Managers who agree to participate and provide online consent will create their individual *HeadCoach* registration account and complete a baseline assessment questionnaire. Demographic details and self-reported information on mental health literacy, attitudes towards mental health issues, confidence in dealing with mental health issues within the workplace, managerial practices used to support the mental health needs the team, and demographic details will be collected. Managers in the intervention group will then be directed into the online *HeadCoach* manager training program while those managers in the control group will be advised they will receive access to the training after a waiting period.

Post intervention questionnaires will be disseminated by email to the intervention and control groups at 6-weeks after completion of the baseline questionnaire. This 6-week period comprises the training period allocated to managers to complete *HeadCoach*. If a manager finishes all components of the online program earlier in the 6-week training period, they will be invited to complete the questionnaire at that earlier point of completion. This approach is expected to prevent non-response and ensure an accurate measure of the post intervention effect.

At the 4-month post-baseline assessment, a final data collection for the primary outcomes and other measures will be conducted for all managers and employees participating in the trial. An email will be sent to all manager and employee level participants inviting them to complete the final questionnaire, and to advise of a prize draw offered for its completion. Managers who complete the 4-month post questionnaire will be entered into a separate prize draw from the employees, for one of three $250 vouchers. Following the completion of all data collection, managers in the waitlist control group will be provided with online access to the *HeadCoach* program.

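### Time to finish training and to the linked assessment, which arises after randomisation and is tied to arm, may enter the treatment-effect models, and nothing confines it to a sensitivity analysis

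*Protocol article*

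**What the plan says.** The Statistical analysis section sets out an intention-to-treat primary analysis, "retaining all participants as randomised, regardless of extent of engagement with training or withdrawal from the study". It uses MMRM, and the change from baseline to 4 months tests the primary hypothesis. Near the end of that same paragraph it adds: "Length of time from baseline to complete training and associated post-intervention assessment will also be introduced tentatively into models". The sentence gives its purpose as "to evaluate the effects of adjustment for possible effects associated with some managers undertaking these assessments earlier than others and earlier than control group participants". Secondary manager outcomes come in the next paragraph and are to be analysed in a similar way.

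The timing difference is built into the procedure (Trial procedure and assessment, Managers). The general rule is: "Post intervention questionnaires will be disseminated by email to the intervention and control groups at 6-weeks after completion of the baseline questionnaire". For managers who finish the program sooner, "they will be invited to complete the questionnaire at that earlier point of completion". Controls cannot finish sooner: "Following the completion of all data collection, managers in the waitlist control group will be provided with online access". On blinding, the Statistical analysis section says: "A member of the research team who is blinded to the intervention and waitlist control allocations will perform this analysis".

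**The concern.** How fast a manager finishes the program is a form of engagement. It arises after randomisation and can occur only where training was offered. Adjusting a treatment effect for it sits badly with a promise to analyse everyone whatever their engagement. Control assessment times lie near 6 weeks, so the adjusted arm coefficient compares controls with intervention managers at about that same time, who are the late finishers and non-finishers. That is not the effect in all randomised managers.

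Three things are at stake: what the primary contrast estimates, its precision in a trial powered at 80% for 0.54 SD, and the blinding of the analyst.

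**Working it through.** **1. Who has which time (Managers section)**

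| Group | Training-completion time | Post-intervention assessment time |
|---|---|---|
| Control | none during the trial | about 6 weeks |
| Intervention, not finished | none | about 6 weeks |
| Intervention, finished early | yes | can be before 6 weeks |

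A recorded completion time, or an assessment well before 6 weeks, identifies an intervention manager. A model that uses completion time must drop controls and non-finishers or give them an invented value.

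**2. The plan's own power figure (Sample size and power calculations)**

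Inputs are 42 clusters averaging 20 managers, 20% participation, 25% drop-out, intraclass correlation 0.05, effect 0.54 SD and two-sided alpha 0.05.

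- Managers per cluster: 20 × 0.20 = 4. Design effect: 1 + (4 − 1) × 0.05 = 1.15.
- Recruited: 42 × 4 = 168. Followed up: 168 × 0.75 = 126. Effective number: 126 / 1.15 = 109.6.
- SE with equal arms: √(4 / 109.6) = 0.191 SD.
- Power: Φ(0.54 / 0.191 − 1.96) = 0.807 (noncentral t: 0.800). The stated 80% is reproduced.

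**3. Precision if the timing term acts on the 4-month contrast**

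Let intervention managers be assessed on average d weeks before controls, with SD s weeks, and hold control time constant. With n per arm and residual variance σ², the variance of the adjusted arm coefficient is σ²[2/n + d²/(n s²)]. This is the unadjusted variance times 1 + d²/(2s²). Power is Φ(0.54 / (0.191 × SE ratio) − 1.96). The documents give neither d nor s, so the values below are assumptions.

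| d | s | Variance factor | SE ratio | Power |
|---|---|---|---|---|
| 0.5 | 1.0 | 1.125 | 1.06 | 0.759 |
| 1.0 | 1.5 | 1.22 | 1.11 | 0.725 |
| 1.0 | 1.0 | 1.50 | 1.22 | 0.636 |
| 1.5 | 1.5 | 1.50 | 1.22 | 0.636 |
| 2.0 | 1.5 | 1.89 | 1.37 | 0.538 |
| 2.0 | 1.0 | 3.00 | 1.73 | 0.371 |

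Two concrete timing patterns fall inside this range:

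- If 30% finish early, uniformly over weeks 1 to 6, and the rest are assessed at week 6, then d = 0.3 × 2.5 = 0.75 and s² = 0.3 × 8.33 − 0.75² = 1.94. The factor is 1.145 and the SE rises by 7%.
- If all intervention times are uniform over 1 to 6.5 weeks and controls sit at 6.2, then d = 2.45 and s = 5.5/√12 = 1.59. The factor is 2.19 and the SE rises by 48%.

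**4. Bias**

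A cluster simulation used 42 clusters of 3, intraclass correlation 0.05, a single outcome and a true effect of 0.54. The share finishing early was assumed to be 25% or 50% of the intervention arm.

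- Early finishing unrelated to outcome: no bias, SE ratio 1.07 to 1.16, power 0.75 to 0.70.
- Early finishers would have scored better anyway (assumed motivation–outcome correlation 0.2 to 0.4): the adjusted effect falls to between 0.49 and 0.36, and power to between 0.70 and 0.40.
- Same associations, true effect zero: the adjusted estimate shifts to between −0.05 and −0.18. Rejection is 6% to 14%, against 5% to 6% unadjusted.

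**5. Does this reach the planned contrast?**

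A three-visit simulation (baseline, 6 weeks, 4 months) used 110 managers, visit correlation 0.5, half the intervention arm finishing early, and a motivation effect of 0.3 SD at both follow-ups. All of these are assumed. It compared ways of entering the term, with complete data and with 25% missing at 4 months.

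| How timing enters | 4-month effect | SE ratio |
|---|---|---|
| Not entered | 0.54 | 1.00 |
| Person-level main effect | 0.54 | 1.00 |
| Time-varying actual assessment time | 0.54 | 1.00 |
| Time by visit | 0.40 | 1.15 to 1.19 |
| Covariate in a change-score model | 0.40 | 1.19 to 1.25 |

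The article does not say how the term enters. Its abstract defines the primary outcome as change from baseline, so a change-score model is a realistic possibility.

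**The case against.** The strongest reply is that the sentence describes a check. Its stated purpose is to evaluate what adjustment does, which reads naturally as fitting the model with and without the term. That exploratory reading is open. But the sentence stands in the primary-analysis paragraph, is not labelled a sensitivity analysis, and is not tied to the 6-week visit.

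Stronger readings are tempting, and the documents do not support them:

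- A reader might infer that significance decides whether timing stays. The rule "tentatively included in these models and retained if statistically significant and influential on outcomes" belongs to the preceding sentence, on stratification and imbalanced variables. No retention rule is given for timing.
- A reader might infer that the variable exists in one arm only. That is true of training-completion time. Controls and non-finishers do have an assessment time.
- A reader might infer that the primary result will be biased and imprecise. The 4-month assessment is not moved by early completion, and two of the four ways of entering the term leave the contrast intact. Bias also needs a link between finishing speed and outcome, whose size and direction the documents do not give.
- A reader might take a large SE penalty as typical. The 48% case has nearly every intervention manager finishing early, while the Discussion itself warns of low completion rates. A gap nearer 7% is just as compatible with the text.

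On blinding, the planned per-protocol analyses also need completion data, so the problem is not peculiar to this covariate. That makes it a matter of sequencing but does not remove it.

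**Conclusion.** The point holds in a limited form. The article permits a post-randomisation, arm-dependent variable in its treatment-effect models without confining it to a sensitivity analysis. That conflicts with its intention-to-treat statement, and handing the variable to the analyst undermines the stated blinding.

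The harm to the 4-month result is conditional. With a time-by-visit term or a change-score model, the SE rises by about 6% to 73% and power falls from 0.80 to between 0.76 and 0.37, over timing gaps averaging 0.5 to 2 weeks. Bias is added if speed and outcome are related; in the three-visit simulation the effect moved from 0.54 to 0.40. With a person-level main effect or time-varying assessment time in a raw-score MMRM, the 4-month contrast is unaffected. Timing gaps, spreads and associations are all assumptions. The conflict with intention-to-treat and blinding does not depend on them.

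**What to change.** - State that training time and assessment time are excluded from the primary 4-month model and from the main models of secondary outcomes.
- Confine actual assessment time to a sensitivity analysis of the 6-week outcome, labelled as such.
- Release timing and completion data to the analyst only after the blinded primary analysis is final. The per-protocol analyses then follow the same sequence.
- Report the 6-week contrast with an explicit note that assessment timing differs between arms.

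Do not restrict the 6-week analysis to a common assessment window. That would remove fast finishers from one arm only and so select on the same post-randomisation variable. The send date can stay as it is: the article gives a reason for early invitations, and Trial status says data collection is under way.

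The cost is slightly more sequencing of the analysis and one fewer adjusted model. No new data are needed, and the stated 80% power is kept.

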### Intervention

The *HeadCoach* online training intervention aims to build managers’ confidence in dealing with mental health issues in the workplace. This includes managers’ confidence when responding to mental illness and/or distress amongst their staff, and the implementation of behaviours supporting more mentally healthy workplaces to help prevent new mental health problems. Building confidence across these reactive and preventative managerial strategies to better manage mental health issues in the workplace is a key step in altering managers’ behaviours across these domains [21]. Improving confidence is also one of the central concepts of Self-Efficacy Theory, which suggests that people are more likely to engage in particular behaviours across a range of settings when they feel more capable of successfully attaining the intended outcome [22].

The intervention is self-guided and divided into three broad topics to be completed sequentially. The first topic, *Common mental illnesses*, provides an introduction to mental health issues commonly found in the workplace. The next topic, *How to help an employee you are concerned about*, discusses ways managers can identify people within their team who may be at risk of mental health issues, how managers can support their workers, and direction around how to best have a conversation with employees who may be experiencing mental ill health. It also discusses how to help employees stay at work or return to work faster following a period of sickness absence due to mental illness. The third and final topic, *Minimising mental health risks in the workplace,* examines managerial skills that are useful in reducing mental health risk factors in the workplace in order to create a mentally healthy workplace for all employees.

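### The per-protocol dose comparison pools partial and full completers, so it cannot answer its subset-versus-complete question, and its companion comparison with waitlist responders is non-randomised and should be labelled so

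*Protocol article*

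**What the plan says.** All of this is in the Statistical analysis section of the protocol article unless noted.

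- The primary analysis is by intention to treat, whatever a manager's engagement with the training, and tests change from baseline to 4 months.
- A further set of analyses is then defined: "Additional per-protocol analyses to assess effectiveness of the program will focus on managers who completed at least one of the three topics".
- The comparators follow: "This subgroup will be compared to all responders in the waitlist control group and, secondarily, with managers who completed less of the training material".
- The second comparison has a stated purpose: "The latter comparison will inform the dose-response profile of the intervention". In particular it is to show "whether completing only a subset of the earlier components" brings a benefit comparable to that of the whole program.
- The Intervention section says how exposure arises: "The intervention is self-guided and divided into three broad topics to be completed sequentially". Table 1 lists 2, 6 and 4 content modules in Topics 1, 2 and 3.

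**The concern.** There are two separate problems.

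**The dose contrast.** The reference group is everyone with one or more topics, so managers who did less can only be those below one topic. Because topics are taken in order, the reference group mixes managers who stopped after Topic 1, managers who stopped after Topic 2, and managers who finished. The question concerns a difference inside that group, while the contrast compares the group with people outside it. A reader could take the result as evidence on whether a shortened course is enough when it carries none.

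**The comparison with the waitlist.** Completion is the manager's own choice after randomisation. Intervention managers who did not complete a topic are removed, while waitlist managers who would not have completed one stay in. The two sides are therefore filtered differently, and randomisation no longer protects the contrast. The plan nevertheless presents it as assessing effectiveness and describes no adjustment or caveat specific to it.

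**Working it through.** **The plan's own figure.** The only stated precision is for the primary comparison (Sample size and power calculations). 42 × 20 × 0.20 = 168 recruited; 168 × 0.75 = 126 followed up; managers per cluster 168/42 = 4; design effect 1 + (4 − 1) × 0.05 = 1.15. With 1:1 allocation (an assumption, as the ratio is not stated) there are 63 per arm, or 63/1.15 = 54.8 effective. Power at 0.54 SD, two-sided 0.05, is 80.7% by the normal approximation and 80.0% by the noncentral t. The figure reproduces. No figure is given for the per-protocol or dose comparisons.

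**What the split separates.** Topic 1 holds 2 of the 2 + 6 + 4 = 12 content modules, so the per-protocol group runs from 2 modules to all 12. Assume equal thirds at one, two and three topics, and effects in SD relative to managers below one topic:

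| Profile | 1 topic | 2 topics | 3 topics | Pooled mean | Complete minus mean of 1 and 2 |
|---|---|---|---|---|---|
| Plateau after Topic 1 | 0.54 | 0.54 | 0.54 | 0.54 | 0.54 − 0.54 = 0.00 |
| Linear | 0.27 | 0.54 | 0.81 | 0.54 | 0.81 − 0.405 = 0.405 |
| Benefit only on completion | 0 | 0 | 1.62 | 0.54 | 1.62 − 0 = 1.62 |

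The planned contrast sees only the pooled column. The last column, which is the stated question, does not enter it, and a larger sample would not help.

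**Precision of a contrast that does address the question.** Compare one or two topics with all three in the intervention arm: half-width = 1.96 × √(1/a + 1/b), where a is the number with all three topics and b the number with one or two. For the design effect, multiply the variance by 1.15.

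- All 63 complete a topic and 20% of them finish: a = 12.6, b = 50.4, half-width 0.62 SD (0.66 with the design effect).
- All 63 complete a topic and 50% finish: a = b = 31.5, half-width 0.49 SD (0.53).
- Only 70% of the 63 complete a topic: 0.59 to 0.74 SD (0.63 to 0.79) over the same shares.

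The range is therefore roughly 0.5 to 0.8 SD. The completion shares are assumptions, as the documents give none.

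**Selection against the waitlist.** Let p be the share who complete a topic and D the difference, in SD, between the change completers and non-completers would show without training. Completers' untrained change exceeds the whole-arm mean by D − pD = (1 − p)D. With no true effect, that is the bias against an unselected control arm. For illustration, p = 0.5 with D = ±0.3 gives ±0.15 SD, and p = 0.3 with D = ±0.5 gives ±0.35 SD. Against managers below one topic the bias is D in full. Neither p nor D, nor the sign of D, is in the documents. If waitlist responders are themselves a selected group, their own shift is subtracted from (1 − p)D.

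**The case against.** The strongest reply is that nothing important hangs on these analyses. They are labelled additional, and the primary analysis keeps everyone as randomised. That stands. A reader might infer that the trial's main conclusion is compromised; the document does not support that.

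A reader might also infer that the waitlist comparison will come out positive under no effect simply because completers are more confident managers. That does not follow. The planned outcome is change from baseline, and no different model is given for the per-protocol analyses, so a stable difference in level cancels. Bias needs a difference in change unrelated to the training. Its direction is open: less confident managers may have more reason to finish and more room to rise on the 6 to 30 scale. The Discussion also expects that waitlist dropout may be higher, so the waitlist responders may be a motivated subset too, which would offset part of any gap. What remains is that the contrast is unprotected, not that it is biased by a known amount.

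On dose, it can be said that speaking of a dose-response profile implies graded levels, and that cut-points are left to an analysis plan. But the article does fix the comparison: it names the reference group, names the comparator and states what the result will show. Those three do not fit together. It is equally fair that a split by topics would be too imprecise to establish comparability, and the remedy has to say so.

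Finally, a complier analysis is not a clean replacement. With a one-topic threshold, managers who did some modules but less than a topic were still exposed, so the exclusion restriction fails. Zones were randomised before recruitment and managers opted in afterwards (Study design; Recruitment process), so the instrument relies on consent not differing by arm.

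**Conclusion.** The mismatch between the dose contrast and its stated question holds on the text and needs no numerical assumption: partial and full completers are on the same side of the split. The 0.54 SD illustration assumes equal thirds.

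The comparison with waitlist responders is non-randomised and open to selection after randomisation. This supports a change of label and an added analysis. It does not support a claim about how large the bias is or which way it runs; the ±0.15 and ±0.35 SD values show only how the formula behaves under chosen inputs.

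The point should be corrected, but it is confined to the additional analyses. The primary result stands as planned.

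**What to change.** 1. **Dose.** Within the intervention arm, report change from baseline by topics completed (under one, one, two, three), with an explicit contrast of partial with full completion, adjusted for baseline confidence. Label it observational and describe it by its confidence interval only, stating that a half-width of roughly 0.5 to 0.8 SD, against the 0.54 SD the trial is sized for, cannot establish comparable benefit. Alternatively, delete the subset-versus-complete statement.
2. **Waitlist comparison.** Call it exploratory and non-randomised, not an assessment of effectiveness.
3. **Alongside it**, add a complier average causal effect with zone allocation as the instrument, allowing for clustering. Use any uptake of the training as the exposure, or state the assumption of no benefit below one topic. State also the assumption that consent did not differ by arm. Waitlist managers receive access only after all data collection (Trial procedure, Managers), so non-compliance is essentially one-sided, apart from the contamination that the Discussion acknowledges.

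The cost is a few sentences, a little more analysis on adherence data the research platform already records, and a wider interval than the completer comparison would give. The primary analysis does not change.
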